**Methods and analysis:**

We will conduct a single-centre, two-group, single-blind randomised controlled trial with 42 participants who have sustained a cervical or thoracic SCI within the past year. The non-intervention group will receive hospital standard of care (control group) while the intervention group will receive hospital standard of care plus moderate-intensity ACET for 10 weeks in line with the SCI-specific exercise guidelines to improve cardiometabolic health. The primary outcome measure will be central arterial stiffness (carotid-to-femoral pulse wave velocity). Secondary outcomes include assessments of (1) blood biomarkers linked to CVD, (2) cardiac structure and function, (3) extracranial vasculature, (4) HRQOL, (5) cognitive function, (6) physical activity level, (7) cardiorespiratory fitness, (8) motor function and (9) feasibility outcomes. Assessments will occur at baseline (rehabilitation centre admission, −2 weeks), preintervention (0 weeks), postintervention (10 weeks) and follow-up (6 months after postintervention), for HRQOL outcomes only.

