### Eligibility criteria

#### Randomisation

After preintervention assessments (A1 and A2), recruited participants will be randomly allocated into one of the two study groups using a computer-generated randomiser. Figure 1 provides an overview of the trial flow, illustrating the sequence of assessments, randomisation and subsequent testing. The A1 and A2 assessments are conducted prior to randomisation to gather initial data on participants to understand initial status and variability among participants. Conducting randomisation after these assessments minimises the risk of allocation bias, which could occur if knowledge of group assignment influenced initial measurements. Randomisation will be performed by an independent researcher ([name]) not involved in the recruitment process to minimise selection bias. Block randomisation methods will be used to ensure balance in group sizes. In consultation with the Director of Statistics and Research Strategy at the Birmingham Clinical Trials Unit, it was determined that any imbalances of the participants recruited to the study would be down to chance. Each participant will be assigned a unique participant identification number and the corresponding trial group will be provided according to the list. Blinding is not achievable during data collection, therefore, neither participants nor data collectors will be blinded. However, to minimise bias, data analysts will be blinded to participant allocation.

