Adherence will be periodically assessed every 3 weeks to determine the feasibility of the participant achieving the minimal amount of exercise sessions during the 10-week period. This pragmatic approach accounts for the associated complexities of working with this population in the subacute setting that may result in exercise sessions being missed. Participants will be given the option to catch up with missed exercise sessions during subsequent weeks. If a participant misses a period of 3 weeks’ worth of consecutive exercise sessions (n=9) and is unable to compensate after review with a member of the study team, then they will be withdrawn from the trial due to non-compliance (figure 2).

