### Assessments

Following the provision of informed consent (see ‘Participant consent form’; online supplemental file 1), outcomes will be assessed at four time points: (A1) baseline (−>2 weeks), (A2) preintervention (0 weeks), (A3) following the ACET or standard care (postintervention) (10 weeks) and (A4) 6 months after discharge for HRQOL outcomes only (figure 3; table 1).

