Autonomic Dysfunction in Spinal Cord Injury	X						X	
Primary Outcome								
Carotid-Femoral Pulse Wave Velocity		X		X			X	
Secondary outcomes								
Blood sampling		X		X			X	
Health-Related Quality of Life Standard Questionnaires		X		X			X	X
Digit Span and Symbol Digit Modalities Test		X		X			X	
Wheelchair Users Shoulder Pain Index		X		X	X(weekly)		X	X
Cardiovascular Ultrasound		X		X			X	
Resting heart rate variability		X		X			X	
24-hour ambulatory blood pressure monitoring			X			X		
Rehabilitation energy expenditure (>3 days of monitoring) and free-living heart rate variability			X			X		
Motor function testing			X				X	
Arm cycle exercise familiarisation			X					
Cardiorespiratory fitness and heart rate recovery				X			X	
Continuous exercise heart rate and episodic (pre/post) Blood pressure monitoring					X(all sessions)			
Feasibility and Acceptability Questionnaire							X	
One-to-one Interview							X	

* For the A4 time point, only Health -Related Quality of Life Questionnaires and WUSPI will be completed.

Cardiorespiratory fitness assessments commence at A2 following a 20 min familiarisation session on the arm-crank ergometer, which will be performed by all participants between A1 and A2 (see table 2). The duration between A1 and A2 will be at least 2 weeks, although this timeframe is flexible based on the clinical needs of the patient. For example, prolonged bed rest may necessitate a longer interval before initiating standard of care rehabilitation due to factors such as fatigue or secondary complications such as pressure sores or urinary tract infections. At A4, occurring 6 months after A3 (ie, postintervention), we will remotely reassess HRQOL outcomes to determine whether there are differences between the ACET and CON groups.

A1, A2 and A3 assessments will be carried out within MCSI at the RJAH. A4 follow-up assessments will be conducted virtually. To ensure fidelity of assessments, the CI and research personnel held initial meetings for standardised training and logistics. Regular executive committee meetings consisting of the CI ([name]), site PI ([name]), site clinical lead ([name]), postdoctoral research fellow ([name]), research nurse, healthcare assistant and other MCSI staff will convene to discuss any data collection issues or safety issues that arise.

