### Power calculation and sample size

We aim to recruit 42 participants for this study. This sample size was based on the effect size drawn from the CHOICES multicentre RCT.^129^ Our a priori power calculation indicated that a sample size of 32 individuals with SCI, 16 in each group, is sufficient to detect a between-group interaction effect for cfPWV, using a two-way repeated measures ANOVA with 95% power and a 5% level of significance to detect exercise group differences of ≥1 m/s. Our target effect size of 1 m/s aligns with reported exercise intervention effects in high-risk populations and represents a clinically meaningful improvement, as each 1 m/s increase in cfPWV corresponds to a 15% increased risk of cardiovascular mortality.^130 131^ A recent study found that ~16% of participants who were randomly assigned to a 5-week ACET intervention in the subacute setting discontinued the intervention.^132^ To account for the longer intervention duration in this trial, a more conservative (30%) dropout rate was estimated. Hence, 42 participants in total will be enrolled in the study.

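### ACET participants who miss nine consecutive sessions and cannot make them up leave the trial, not only the exercise, so post-randomisation removal falls on one arm and their A3 outcome is lost

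*Protocol article*

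**What the plan says.** The rule is at the end of the section on arm cycle ergometry training. It has two conditions: the participant has missed three weeks' worth of "consecutive exercise sessions (n=9) and is unable to compensate after review with a member of the study team". Before it applies, missed sessions can be made up: "Participants will be given the option to catch up with missed exercise sessions during subsequent weeks". Its consequence is stated for the trial as a whole: "then they will be withdrawn from the trial due to non-compliance".

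Three other statements fix how the rule works:

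- **Arms (Abstract, Methods and analysis).** "The non-intervention group will receive hospital standard of care (control group") and no exercise sessions are prescribed for it. The article states no compliance rule for that arm.
- **Timing (Randomisation).** "After preintervention assessments (A1 and A2), recruited participants will be randomly allocated into one of the two study groups". Any withdrawal for missed sessions is therefore a post-randomisation event.
- **Outcome (Assessments and Table 2).** cfPWV is measured at A1, A2 and A3. A1 and A2 precede allocation, so A3 ("A3) following the ACET or standard care (postintervention) (10 weeks") is the only primary measurement after it. A4 collects quality-of-life questionnaires and shoulder pain only.

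Nothing in the article says that a participant withdrawn under this rule still attends A3 or A4.

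**The concern.** The stated objective is to compare ACET added to standard care with standard care alone. Randomisation protects that comparison only if the two groups are followed and analysed as allocated. Here, behaviour after allocation decides who is measured, and it can do so in one arm only. A control participant who would have been unable to train for three weeks stays in and is assessed, while the counterpart in ACET is not. The data then compare ACET participants who could keep training with everyone in control.

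If those who cannot train would have had a worse cfPWV change in any case, their removal flatters ACET and raises the false-positive rate. The A4 comparison is affected in the same way. The rule also takes the least adherent participants out of the A3 feasibility questionnaire and interviews, although one purpose of the flexible prescription is to learn what volume inpatients can realistically achieve.

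**Working it through.** **1. Can the rule reach both arms?** No. The trigger is missed prescribed sessions, and only ACET has them. This follows from the text and needs no assumption.

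**2. Size of the shift.** Let m be the mean cfPWV change of ACET participants who are retained, p the share of ACET withdrawn under the rule, and D the amount by which the withdrawn participants' change would be worse (higher).

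- Mean if all are followed: (1 − p)·m + p·(m + D) = m + p·D
- Mean actually observed: m
- Shift in the ACET − control contrast: −p·D, which favours ACET when D > 0

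**3. Inputs.**

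- Arm size: 42 / 2 = 21. The plan's 42 reproduces as 32 × 1.30 = 41.6, rounded up. Whether that is the right way to allow for dropout is a separate question.
- SD of change: not given. Back-solved from 16 per arm, 95% power, two-sided 5% (sidedness assumed) and 1 m/s. Normal approximation: 1 / [(1.960 + 1.645) × √(2/16)] = 0.78 m/s. With the t distribution: 0.76 m/s, used below.
- p: not given. 10% is assumed. 16% borrows the discontinuation rate of an earlier 5-week study, and 30% borrows the planned dropout. Neither of the last two is the share withdrawn under this rule.
- D: not given. Values of 0, 0.25, 0.5 and 1.0 m/s are assumed. The last equals the trial's whole target effect.

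**4. Results with no true effect.** Each cell gives the bias p × D, then the two-sided type I error. The simulation used 21 per arm, the same share of potential non-compliers in both arms but removal from ACET only, a t test on change, a total SD of 0.76 m/s and 20,000 runs per setting. The D = 0 column is by construction.

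| p | D = 0 | D = 0.25 | D = 0.5 | D = 1.0 |
|---|---|---|---|---|
| 10% | 0; 5% | 0.025; 5.2% | 0.05; 5.4% | 0.10; 6.9% |
| 16% | 0; 5% | 0.04; 5.0% | 0.08; 6.4% | 0.16; 9.8% |
| 30% | 0; 5% | 0.075; 5.8% | 0.15; 8.8% | 0.30; 21% |

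The last cell depends on how the SD is read. If 0.76 m/s is the SD within subgroups, the type I error is about 16%. If it is the total SD, it is 21–22%.

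**5. Power.** For a 1 m/s difference with SD 0.76, power is 98.6% with 21 v 21, 97.9% with 18 v 21 and 96.6% with 15 v 21. The loss of numbers matters little. The harm is selection.

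**The case against.** The strongest defence is that the rule is a last resort. Nine missed sessions alone do not trigger it. Catch-up is offered, a review comes first, and participants discharged early receive an ergometer at home and weekly calls. Few people may be withdrawn, in which case the bias is small: at p = 10% and D = 0.25–0.5 m/s the type I error barely moves. This stands, and it is why the lower rows and columns of the table matter. The added condition does not remove the asymmetry, however, and it may select more strongly for people with a lasting inability to train.

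It can also be said that an unseen analysis plan may define an as-randomised population. It may, but it cannot recover an A3 value that the protocol's rule has stopped anyone from collecting.

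Four stronger readings are tempting and are not supported:

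- **That complications are the documented cause of missed sessions.** The Assessments section does name "secondary complications such as pressure sores or urinary tract infections", but as reasons for a longer interval between A1 and A2, before randomisation. Carrying them over to the training period is inference.
- **That the bias certainly favours ACET.** If sessions are missed through early discharge or low motivation, D could be near zero or of either sign.
- **That the sample size section confirms the loss of assessments.** It cites participants "randomly assigned to a 5-week ACET intervention in the subacute setting discontinued the intervention" and then sets a dropout allowance. That runs the two ideas together, but it does not say that discontinuers in this trial go unmeasured.
- **That continued follow-up would recover much of the planned 30% loss.** Half of 42 × 0.30 = 12.6 is about 6 people. As the rule reaches only ACET, all 6 would have to come from 21 participants, about 29% of that arm. Nothing in the article supports that.

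**Conclusion.** The point holds as a fault in a stated rule. The wording withdraws people from the trial, it acts after allocation, and it can reach only one arm. That A3 and A4 are then not collected is the natural reading, though the article does not say so in terms.

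The size is not known. It rests on p and D, which the documents do not give, and the type I error rests also on a back-solved SD of about 0.76 m/s. Over the illustrative range the bias runs from 0, through about 0.03 to 0.16 m/s (type I error about 5–10%), to a ceiling of 0.30 m/s, or 30% of the 1 m/s target (about 16–22%). The ceiling needs every part of a 30% loss in ACET to come from this rule, together with a D as large as the target effect. The direction is probably in favour of ACET, not certainly.

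**What to change.** Replace the consequence in the rule with wording such as: *recorded as having discontinued the intervention; A3 and A4 assessments are still carried out as scheduled unless consent is withdrawn*. State that these participants are included in the primary comparison in the group to which they were randomised, and that any compliant-only comparison is supplementary. When the exercise itself stops is a clinical matter and is not addressed here.

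The cost is a protocol wording change, a few more assessment visits for people who have already consented, and possibly a smaller as-randomised effect. If non-compliers gain nothing from ACET (assumed) and the SD is 0.76 m/s, a 1 m/s effect becomes 1 × (1 − 0.16) = 0.84 m/s at 16% non-compliance, or 1 × (1 − 0.30) = 0.70 m/s at 30%. With all 21 per arm assessed, the power is about 95% and 85% respectively (normal approximation). In return, the bias from this rule is zero and the type I error stays at 5%.

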### Assessments

Following the provision of informed consent (see ‘Participant consent form’; online supplemental file 1), outcomes will be assessed at four time points: (A1) baseline (−>2 weeks), (A2) preintervention (0 weeks), (A3) following the ACET or standard care (postintervention) (10 weeks) and (A4) 6 months after discharge for HRQOL outcomes only (figure 3; table 1).

**Figure 3 F3:**
[figure not shown]
Study flow chart. Following participant identification and initial assessments (**A1**) at MCSI, assessments will be repeated after a period of standard care (which will primarily involve bed rest depending on the severity of injury) (**A2**). Participants thereby act as their own controls. At this point, participants will be randomised to receive either standard of care inpatient rehabilitation (CONTROL) or standard of care inpatient rehabilitation plus 30 min of ACET, 3–5 times per week (ACET INTERVENTION) for 10 weeks, with postassessments (**A3**). 6 months after discharge (~36 weeks) into the community, follow-up HRQOL assessments will be carried out (**A4**). ABPM, ambulatory blood pressure monitoring; ACET, arm-crank exercise training; HRQOL; health-related quality of life; SCI, spinal cord injury.

The A1 assessment serves as a time point for characterising key outcome measures on admission into inpatient rehabilitation, providing a baseline of cardiovascular health. Given the significant adjustments participants face following this life-changing injury, we have streamlined some of the secondary outcome measure assessments between A1 and A2 to minimise participant burden. Therefore, rehabilitation physical activity energy expenditure, 24-hour BP monitoring and motor function assessments will be conducted only once between A1 and A2, as outlined in table 2. The rationale for having both A1 and A2 assessments for the cardiovascular measures and HRQOL questionnaires is twofold: (1) to gauge any variability or changes in responses between the time close to admission (A1) and the adjustment to their new injury (A2; for example, following initial standard of care therapy sessions) and (2) to establish multiple baselines for these outcome measures, thereby allowing participants to serve as their own controls and capturing the inherent variability in these outcomes.

**Table 2 T2:** Schedule of enrolment, interventions and assessments

Study procedures	Screen	Baseline(A1)	A1–A2	Preintervention/randomisation(A2)	Training sessions	Final week	Postintervention(A3)	Community follow-up(A4)*
Visit (V)	V1	V2	V2/V3	V3/V4	V4/V5–V45/V46	V46/V47	V47/V48	V48/V49
Eligibility								
Informed consent	X							
Medical history/demographics	X							
Changes in medication/health status				X			X	
Pregnancy screening	X							
International Standards for Neurological Classification	X						X	
Autonomic Dysfunction in Spinal Cord Injury	X						X	
Primary Outcome								
Carotid-Femoral Pulse Wave Velocity		X		X			X	
Secondary outcomes								
Blood sampling		X		X			X	
Health-Related Quality of Life Standard Questionnaires		X		X			X	X
Digit Span and Symbol Digit Modalities Test		X		X			X	
Wheelchair Users Shoulder Pain Index		X		X	X(weekly)		X	X
Cardiovascular Ultrasound		X		X			X	
Resting heart rate variability		X		X			X	
24-hour ambulatory blood pressure monitoring			X			X		
Rehabilitation energy expenditure (>3 days of monitoring) and free-living heart rate variability			X			X		
Motor function testing			X				X	
Arm cycle exercise familiarisation			X					
Cardiorespiratory fitness and heart rate recovery				X			X	
Continuous exercise heart rate and episodic (pre/post) Blood pressure monitoring					X(all sessions)			
Feasibility and Acceptability Questionnaire							X	
One-to-one Interview							X	

* For the A4 time point, only Health -Related Quality of Life Questionnaires and WUSPI will be completed.

Cardiorespiratory fitness assessments commence at A2 following a 20 min familiarisation session on the arm-crank ergometer, which will be performed by all participants between A1 and A2 (see table 2). The duration between A1 and A2 will be at least 2 weeks, although this timeframe is flexible based on the clinical needs of the patient. For example, prolonged bed rest may necessitate a longer interval before initiating standard of care rehabilitation due to factors such as fatigue or secondary complications such as pressure sores or urinary tract infections. At A4, occurring 6 months after A3 (ie, postintervention), we will remotely reassess HRQOL outcomes to determine whether there are differences between the ACET and CON groups.

A1, A2 and A3 assessments will be carried out within MCSI at the RJAH. A4 follow-up assessments will be conducted virtually. To ensure fidelity of assessments, the CI and research personnel held initial meetings for standardised training and logistics. Regular executive committee meetings consisting of the CI ([name]), site PI ([name]), site clinical lead ([name]), postdoctoral research fellow ([name]), research nurse, healthcare assistant and other MCSI staff will convene to discuss any data collection issues or safety issues that arise.

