### Statistical analysis

The Shapiro-Wilk test will be used to test the distribution of the continuous variables for demographic and outcome measures. Continuous variables will be reported as mean±SD for normally distributed data or median with IQRs for non-normally distributed data; categorical variables will be reported as frequency. Specific injury characteristics will be considered for subanalysis (ie, injury level, injury severity). A two-way repeated measures analysis of variance (ANOVA) will be applied to examine the main effects of the group/time and group–time interaction. Post hoc analyses will be conducted where significant group-time interaction effects are identified. Significance level will be set at 0.05 for all statistical tests. Standardised effect sizes (Cohen *d*) will also be calculated and interpreted based on the following criteria: small (*d*=0.2), medium (*d*=0.5) and large (*d*=0.8) effects.^128^

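### The 6-month (A4) comparison of the arms on quality of life has no test of its own: its only stated inferential route is a post hoc comparison conditional on a significant group-time interaction

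*Protocol article*

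**What the plan says.** In the protocol article, the Assessments section states that "outcomes will be assessed at four time points": A1 and A2 before randomisation, A3 at 10 weeks, and A4 as a follow-up for quality of life. The note under Table 2 confirms the limit: "For the A4 time point, only Health -Related Quality of Life Questionnaires and WUSPI will be completed". The text after that table gives the purpose of A4, a remote repeat of the quality-of-life measures "to determine whether there are differences between the ACET and CON groups".

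Statistical analysis sets out one inferential procedure for all outcomes: "A two-way repeated measures analysis of variance (ANOVA) will be applied to examine the main effects of the group/time and group–time interaction". It continues: "Post hoc analyses will be conducted where significant group-time interaction effects are identified". On the error rate it says: "Significance level will be set at 0.05 for all statistical tests". The same section also promises descriptive summaries and standardised effect sizes, and ties neither to the interaction result. It names no A4 contrast and does not list the visits that enter each model.

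**The concern.** The purpose given for A4 is a between-arm question at one visit. The interaction test asks something broader: whether the pattern of arm differences changes anywhere across the visits. With four visits it has 3 degrees of freedom, and one of them compares A1 with A2, where treatment cannot have acted. The other between-arm test, the group main effect, averages over those same two pre-randomisation visits and so dilutes any A4 difference.

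As written, a comparison of the arms at A4 is therefore reached only through a test that is not aimed at A4. If the interaction misses 0.05, the article offers no formal answer and no interval for the only question asked after the 10-week visit. In a trial of this size a reader could then take a non-significant omnibus test as evidence of no lasting difference.

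**Working it through.** **Plan's own figure.** None exists for A4. Power calculation and sample size states that "a sample size of 32 individuals with SCI, 16 in each group, is sufficient to detect a between-group interaction effect for cfPWV", and cfPWV is not measured at A4. I take 16 per arm from there.

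**Inputs.** From the article: four visits, alpha 0.05, and 0.5 and 0.8 SD as its own labels for medium and large effects. Assumed, because the article gives no values: compound symmetry, visit correlation ρ of 0.5 or 0.7, and an effect that is absent at A1 and A2 and is, at A3, zero, half or all of the A4 effect d.

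**Step 1: how often the interaction is non-significant.** With n per arm, the noncentrality is λ = n·S / [2(1−ρ)]. Here S is the sum over visits of the squared deviations of the arm differences from their mean. S equals 0.75d² (A4 only), 0.6875d² (half at A3) or 1.0d² (equal at A3 and A4). The reference distribution is F with 3 and 3 × (32 − 2) = 90 df, critical value 2.706. Example: A4 only, ρ = 0.5, d = 0.8 gives λ = 16 × 0.75 × 0.64 / (2 × 0.5) = 7.68.

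| Pattern | ρ | λ, d = 0.5 | Non-significant | λ, d = 0.8 | Non-significant |
|---|---|---|---|---|---|
| A4 only | 0.5 | 3.00 | 74% | 7.68 | 39% |
| Half at A3 | 0.5 | 2.75 | 76% | 7.04 | 43% |
| Equal at A3 and A4 | 0.5 | 4.00 | 66% | 10.24 | 25% |
| A4 only | 0.7 | 5.00 | 58% | 12.80 | 15% |
| Half at A3 | 0.7 | 4.58 | 61% | 11.73 | 19% |
| Equal at A3 and A4 | 0.7 | 6.67 | 45% | 17.07 | 6% |

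Simulation of the full model gives 46-76% and 6-44%, the same within simulation error.

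**Step 2: the group main effect.** At 16 per arm and d = 0.5 its power is 7-14%, so it does not stand in for an A4 test.

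**Step 3: cost of the condition, like for like.** The A4 contrast is an ANCOVA on the mean of A1 and A2, simulated with and without the requirement of a significant interaction, at 16 per arm. The requirement costs about 11-20 percentage points of power at d = 0.5 and 3-21 points at d = 0.8.

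**Step 4: the plan as written against the fix, d = 0.8.** As written (significant interaction, then a significant unadjusted A4 comparison), power is about 41-50% at ρ = 0.5 and 53-56% at ρ = 0.7. The adjusted, unconditional contrast reaches 74-75% and 91%. Only the Step 3 share of that gap belongs to the condition. The rest comes from adjustment, which reduces the residual variance to 1 − 2ρ²/(1+ρ) of its unadjusted value: 1 − 0.5/1.5 = 0.67 at ρ = 0.5, and 1 − 0.98/1.7 = 0.42 at ρ = 0.7.

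**Step 5: sensitivity to sample size.** With 21 per arm and no dropout, A4 goes untested in 31-69% of trials at d = 0.5 and 2-29% at d = 0.8. If 30% of 42 are lost (42 × 0.70 = 29.4, about 15 per arm), the figures at d = 0.8 are about 30-47% at ρ = 0.5 and 8-22% at ρ = 0.7.

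**The case against.** Testing visit-level differences only after a significant interaction is conventional, and it filters chance findings. With no true effect and 16 per arm, the adjusted A4 contrast is significant in about 5% of simulated trials when tested unconditionally, against about 1.5-1.9% behind the interaction. The A4 outcomes are secondary, and the trial was not sized for them. The four-visit model is inferred from the schedule. A separate analysis plan, not shown, might add an A4 contrast.

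Most of this stands as a limit on weight, but none of it supplies an A4 test. The article does not leave the matter open: it states a rule, and the rule serves the stated purpose of A4 poorly. A model with fewer visits would still place A4 behind its interaction.

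Three stronger readings are tempting and are not supported:
- A reader might infer that a non-significant interaction leaves no A4 estimate at all. Statistical analysis promises descriptive summaries and Cohen d without that condition, though it does not say for which contrast. What is missing is the formal test and the interval.
- A reader might charge the whole gap in Step 4 to the condition. Much of it comes from baseline adjustment: at correlation 0.7 the condition accounts for the smaller part.
- A reader might infer that any real difference will usually go untested. For 0.8 SD at correlation 0.7 the interaction is missed in only about 6-19% of trials.

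**Conclusion.** The point holds as a mismatch between the stated purpose of A4 and the only inferential route to it. A true A4 difference of 0.5 SD would often get no formal between-arm test. For 0.8 SD this depends on the visit correlation and on how much of the effect is already present at A3. The loss due to the condition alone is material at 0.5 SD and ranges from slight to material at 0.8 SD.

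The sizes rest on assumed correlations, compound symmetry and effect patterns that the article does not give. An unconditional A4 test is itself weak at this sample size, with power of about 37-55% at 0.5 SD. That is a further reason to report an estimate with its interval and not to rely on a pass or fail result. The cfPWV analysis and the primary conclusion are untouched.

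**What to change.** In Statistical analysis, name the between-arm difference at A4 in each quality-of-life outcome as its own pre-specified contrast, adjusted for the pre-randomisation values (A1/A2). Report it with a 95% CI whatever the interaction p-value, and label it a secondary analysis. State that the post hoc rule does not govern this contrast.

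The cost is wording only: no new data, visits or participants. The small downside is that these comparisons lose the omnibus test as a filter, so they should be presented as secondary estimates and not as confirmatory findings.
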